**TIMETABLE**

Estimated start: June 2011

Expected completion: August 2012

**BACKGROUND**

Erythropoietin (Epo) is a 34 kDa glycoprotein that is synthesized in the kidneys in response to low oxygen tension. Epo stimulates the formation of new erythrocytes in the bone marrow, while plasma volume is reduced (Lundby et al., 2007). This eventually increases the oxygen-binding capacity in blood.

Recombinant human Epo (rHuEpo) first came on the market in 1989, and is now used to treat uremic and cancer-induced anemia. Because Epo stimulates red blood cell production, and injection of rHuEpo for a prolonged period increases the aerobic capacity by more than 50% (Thomsen et al., 2007), it will continue to be abused by athletes in endurance sports (Barroso et al. 2008; Pascual et al. 2004; Catlin et al., 2008). This despite the fact that rHuEpo was prohibited by IOC already in 1990. It is therefore extremely important to find a sensitive and robust method to detect such abuse. Not only to ensure a fair competition but also to reduce the abuse and the risk of side effects, including increased risk for cardiovascular disease. The existing method for detecting rHuEpo, approved by WADA, is based on differences in the glycosylation degree and pattern between rHuEpo and endogenous Epo (Catlin et al. 2008; Pascual et al., 2004). However, this method is insensitive and relatively expensive (Pascual et al., 2004; Gore et al., 2003). Whether this approach will be effective against new generations of Epo derivatives produced in human cell lines, and thus expresses the same glycosylation degree and pattern as rHuEpo, is still unknown (Gore et al.

2003). In addition, gene doping is also a future drug strategy one will have to deal with. Stable transfection of the Epo gene in tissue has already been shown in animal models (Hojman et al., 2007). Gene doping was therefore in 2003 added to WADA and the IOC's list of "Prohibited Substances and Methods in Sport"(Pascual et al., 2004). This stresses the importance of developing new and more sensitive Epo analysis. Thus, future anti-doping tests should not only focus on detecting rHuEpo and its derivatives, but also on biological markers that change by Epo exposure. Such markers have been studied. Total hemoglobin mass and reticulocyte percentage (_OFFhr-score_) and the so-called blood-passport (Gore et al., 2003) have been suggested as markers for Epo abuse. The problem with the OFF_hr-score_ is that the cut-off values are based on the average population level, and because of large inter-individual differences the cut-off values (upper and lower limit) are very broad, in order to avoid false-positive results. This ultimately leads to a low detection level (Lundby & Robach, 2009; Borno et al., 2010). Also the blood pass, where one follows the athletes’ blood values over time, proved not to guarantee a drug free sport (Borno et al., 2010).

Proteomics has proven to be a good way to characterize all proteins expressed in a biological system, such as blood. We have already in a previous study showed that 16 days of treatment with rHuEpo resulted in significant changes in several serum proteins (Christensen et al.

2010). The main objective of this project is to investigate the effect of prolonged rHuEpo treatment on changes in the serum proteome of healthy young men. Furthermore, we want to investigate the effect of rHuEpo and physical activity on these markers, as it is important to elucidate the effect of physical activity, if these markers should be used as anti-doping markers in the future.

Epo receptors are found in a variety of different types of tissues other than the bone marrow, including neurons, astrocytes, microglia, cancer cells, gastric mucosal cells and especially muscle tissue. The effect of Epo in these tissues still needs to be fully elucidated.

Furthermore, in this study we also want to look at the effects Epo has on fat and muscle tissue and possible effects on substrate metabolism and insulin sensitivity. In a previous study, we have found that rHuEpo acutely might have an effect on fat metabolism (unpublished data). The study also showed that Epo receptors are found in muscle tissue and that prolonged treatment with rHuEpo results in changes in the muscle proteome. These results suggest that Epo may induce a shift in muscle fiber type from a fast glycolytic phenotype to a slower phenotype (data submitted).

**PURPOSE**

To identify new serum biomarkers to detect abuse of rHuEpo. Secondarily, we want to examine the effects of 10 weeks of rHuEpo treatment and training on a wide range of other parameters e.g. turnover of fat, carbohydrate, and protein, muscle type changes, and activation of satellite cells in skeletal muscle.

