**DESIGN**

• The experiment is a single-blind, randomized study.

• 40 subjects in total will be included and randomly assigned to one of the following groups (n = 10);

o Placebo treatment

o Placebo treatment + endurance training

o rHuEpo treatment

o rHuEpo treatment + endurance training

• Subjects are examined before and after 10 weeks of rHuEpo/placebo treatment, and after a 3 weeks washout period.

• EPO (Darbepoietin alpha) (~50IU/kg)/placebo (saline) is administered s.c. twice a week for the first 3 weeks at a dosage of 2x40 μg, and once a week from week 4-10 at a dosage of 20 μg.

• The endurance training will consist of 1 to 1.5 hours of cycling at 65-80% of VO_2_max, 3 times weekly. This was previously shown to cause an increase in maximum oxygen uptake (Midgley et al., 2006).

[figure not shown]

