**Methods:**

• Metabolic profile, hyperinsulineamic eugluceamic clamp, muscle and fat biopsies, blood tests, maximum oxygen uptake, DEXA scan

**Primary end-points:** Proteomics analysis of serum

**Secondary end-points:** Substrate metabolism, fiber typing, and activation of satellite cells

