**SUBJECTS**

A total of 40 healthy young men will be included in the present study. These will be recruited through the web page www.forsøgsperson.dk and various notices on educational institutions in Aarhus (see attached notice).

Because the effect of rHuEpo on some of the required parameters have not previously been elucidated, it has not been possible to make a power calculation. However, from similar studies in our laboratory, it is estimated that approximately 10 subjects in each group is enough to reach statistical power. Furthermore, in a previous study on a group of 8 subjects it was possible to detect significant changes in the proteome 16 days after treatment with rHuEpo (Christensen et al., 2010).

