**STATISTICS**

Group comparisons will be made with standard statistical methods (t-test and ANOVA or equivalent non-parametric tests). Within the groups, a paired t-test or equivalent non-parametric test will be used. A p-value below 0.05 is regarded as a significant result.

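### The stated purpose is to detect Epo abuse, but the only criterion given is p < 0.05 for an average shift, which does not guarantee that a protein separates individuals

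*Protocol*

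**What the plan says.** Protocol, PURPOSE: "To identify new serum biomarkers to detect abuse of rHuEpo". The primary endpoint, listed under Methods in the design section, is "Proteomics analysis of serum"; no particular protein and no performance measure is named.

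Protocol, STATISTICS, gives the whole analysis: "Group comparisons will be made with standard statistical methods (t-test and ANOVA or equivalent non-parametric tests"), then "Within the groups, a paired t-test or equivalent non-parametric test will be used", and "A p-value below 0.05 is regarded as a significant result". The lay description adds nothing to this.

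Protocol, BACKGROUND, says why new markers are needed. For the existing blood score, "because of large inter-individual differences the cut-off values (upper and lower limit) are very broad", and the protocol names low detection as the result. The same section words the main objective more modestly, as the effect of prolonged treatment on the serum proteome, and treats anti-doping use as a future possibility.

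Protocol, DESIGN: 40 men are "randomly assigned to one of the following groups (n = 10"), two groups on Epo and two on placebo, one of each with endurance training. METHODS (Serum) schedules proteomics at baseline and on days 21, 71 and 92.

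**The concern.** Detection is a decision about one person: is this athlete's value, or its change, outside what untreated people show? A t-test, ANOVA, paired t-test or rank equivalent asks a different question, namely whether values are shifted on average. Significance depends on the size of the shift relative to its spread and also on the number of participants, so a moderate shift can pass while the treated and untreated distributions still overlap heavily.

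The protocol sees this problem in the markers it wants to replace, but states no measure that would show whether its own candidates do better. It could therefore announce new detection markers that share the weakness that motivated the trial. The data needed to check this are already planned, including the trained but untreated men who are the most relevant comparison for an anti-doping test.

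**Working it through.** **The plan's own figure.** SUBJECTS judges about 10 per group to be enough, but says "it has not been possible to make a power calculation". With no effect size, SD or target power, the figure cannot be reproduced. The check below is therefore in SD units.

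**Inputs from the protocol.** 10 per group in four groups; 20 versus 20 if the two Epo groups are pooled against the two placebo groups; significance level 0.05.

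**Assumptions.** Two-sided tests; normal values with equal SD in treated and untreated; one protein used alone; specificity of 95% or 99%. Pooling over training is also an assumption, because the protocol does not specify the contrast.

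**Formulas.** Let d be the shift in SD units, on whatever scale the marker is read.

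- Smallest observed shift that is significant: d = t(0.975, df) × √(1/n₁ + 1/n₂). For 10 versus 10: 2.101 × √0.2 = 0.94. For 20 versus 20: 2.024 × √0.1 = 0.64.
- Shift giving 80% power, from the noncentral t distribution: d = 1.32 (10 versus 10) and d = 0.91 (20 versus 20).
- AUC = Φ(d/√2).
- Sensitivity at a fixed specificity = Φ(d − z), with z = 1.645 for 95% and 2.326 for 99%.

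**Results.**

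| Marker | d | AUC | Sensitivity at 95% specificity | Sensitivity at 99% specificity |
|---|---|---|---|---|
| Just significant, 20 v 20 | 0.64 | 0.675 | 16% | 4.6% |
| 80% power, 20 v 20 | 0.91 | 0.740 | 23% | 7.8% |
| Just significant, 10 v 10 | 0.94 | 0.747 | 24% | 8.3% |
| 80% power, 10 v 10 | 1.32 | 0.825 | 37% | 16% |
| For comparison | 3.00 | 0.983 | 91% | 75% |

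Worked line for d = 0.91: Φ(0.91/1.414) = Φ(0.643) = 0.740; Φ(0.91 − 1.645) = Φ(−0.735) = 0.231; Φ(0.91 − 2.326) = Φ(−1.416) = 0.078, and 1/0.078 = 12.8, so about 1 user in 13.

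**Within-group paired test, n = 10.** The smallest significant mean change is 2.262/√10 = 0.715 SD of the change. If untreated men had mean change 0 and the same SD, sensitivity on the change scale would be Φ(0.715 − 2.326) = 5.4% at 99% specificity. The paired test itself has no untreated comparator.

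**What 20 controls can show.** If all 20 placebo participants are classified correctly, the exact two-sided 95% lower limit for specificity is 0.025^(1/20) = 0.832, or 83%.

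**The case against.** **This is discovery work, and an analysis plan that is not at hand may add discrimination measures.** Much of this stands. BACKGROUND places anti-doping use in the future, the lay description only hopes for it, and the purpose is to identify markers, not to validate them. A reader might infer that the protocol treats any significant protein as a working test; no sentence says so. What remains is a mismatch inside the protocol: PURPOSE speaks of detecting abuse, and the one criterion fixed under STATISTICS does not address detection.

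**The planned tests already take spread into account.** Correct. A reader might infer that comparing means ignores between-person spread, or that choosing proteins by p-value yields poorer detectors. Neither is supported. A t-test divides the difference by a term built from the SD, and the paired test uses each man's own baseline, which removes stable differences between men. In the equal-SD normal model used here, with equal group sizes, ranking by p-value from the unpaired t-test gives the same order as ranking by estimated AUC. The Mann–Whitney statistic divided by n₁n₂ is itself the empirical AUC. Nor does the protocol say that it will rank by p-value. The surviving point is narrower: passing a significance threshold does not ensure a shift large enough for detection.

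**The low detection figures are selected.** In part. The 99% specificity is an assumption, and 1 in 13 describes a marker at the 80%-power effect, not every significant marker. Larger effects detect more, several proteins combined might do better, and a stricter threshold would admit only larger observed shifts. For example, Bonferroni over an assumed 100 proteins at 10 versus 10 needs d = 1.89, which gives 33% at 99% specificity. But at 95% specificity a marker with d = 0.91 still misses about three users in four.

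**Discrimination estimated from 40 men will be imprecise.** True; it supports reporting intervals and a modest label.

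**Conclusion.** The concern holds in a limited form. The protocol's sole stated criterion can be met by a protein that does not usefully separate treated from untreated men, although separation is what its purpose and its criticism of existing markers call for. At the shifts the trial would detect with 80% power, AUC is 0.74 (20 versus 20) to about 0.82 (10 versus 10). Sensitivity is about 23% to 37% at 95% specificity and 8% to 16% at 99%. About 3 SD would be needed for 75% detection at 99% specificity.

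These figures rest on normality, equal SD, two-sided tests, a single protein and assumed specificity levels. They show what the criterion allows, not what the trial will find. The tests themselves are suitable for finding proteins that respond to Epo; what is needed is a measure of discrimination beside them and a label that matches the evidence.

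**What to change.** In the protocol's STATISTICS section, keep the planned tests and add:

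1. For each protein significant under those tests, report AUC and sensitivity at 95% specificity, each with a 95% confidence interval. Use change from own baseline at days 21, 71 and 92, comparing the two Epo groups (20) with the two placebo groups, training included (20).
2. Repeat the selection of proteins inside cross-validation, so that discrimination is not judged on the same men who were used to pick the protein.
3. Call significant proteins Epo-responsive candidate markers pending independent validation.
4. State that 20 controls cannot establish high specificity: even 20 of 20 correct gives a 95% lower limit of only 83%.

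Cost: extra analysis only, since the men, visits and proteomics samples are already planned. The intervals will be wide: with 20 controls, a 95% specificity cut-off corresponds to one false positive (1/20 = 5%). Selection within cross-validation may be unstable with 40 men, and the claim becomes more modest.

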**DESIGN**

• The experiment is a single-blind, randomized study.

• 40 subjects in total will be included and randomly assigned to one of the following groups (n = 10);

o Placebo treatment

o Placebo treatment + endurance training

o rHuEpo treatment

o rHuEpo treatment + endurance training

• Subjects are examined before and after 10 weeks of rHuEpo/placebo treatment, and after a 3 weeks washout period.

• EPO (Darbepoietin alpha) (~50IU/kg)/placebo (saline) is administered s.c. twice a week for the first 3 weeks at a dosage of 2x40 μg, and once a week from week 4-10 at a dosage of 20 μg.

• The endurance training will consist of 1 to 1.5 hours of cycling at 65-80% of VO_2_max, 3 times weekly. This was previously shown to cause an increase in maximum oxygen uptake (Midgley et al., 2006).

[figure not shown]

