**Inclusion Criteria:**

• Written consent before study start

• Adult, healthy men

• Age >18 years and <35 years

• Normal weight (BMI: 18-27)

• Untrained (<2 hours of physical activity per week)

• Non smoking

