**SAFETY**

Before enrolling the participants in this trail a general medical examination will be performed.

Throughout the metabolic day a medical doctor and a laboratory technician will be present to make sure that the subjects are well and they will be able to measure vital parameters (blood pressure, pulse, blood sugar levels, and level of consciousness). Medical doctor [name] will perform all invasive procedures, and clinically responsible for the project is [name] [name].

Acute treatment with Epo is not associated with serious side effects, but may be associated with transient flu-like symptoms, which will disappear within a few hours. Prolonged treatment may be associated with increased risk of thrombosis, hypertension and iron deficiency. A protocol similar to the Epo treatment regimen used here, has previously been approved by the Ethics Committee of Copenhagen and Frederiksberg (Lundby et al., 2007; Thomsen et al., 2007; Borno et al. 2010; Juel et al. 2007; Lundby et al., 2008). Here an increase in hematocrit from 45% to 49% (P <0.05) was found (Juel et al., 2007). The risk of thrombosis is greater if the subjects also have hypertension. Subjects will therefore be included only if their blood pressure is normal (<135/85) and they will be excluded if their hematocrit exceeds 55% (present doping limit is 50%, and the limit for venesection 55%). To avoid iron deficiency, all subjects will be treated with 100 mg iron orally daily from 1 week before the start of the experiment until the end.

When obtaining the biopsies there is a very small risk of infection or bleeding in the tissue. The subjects are instructed to contact the person responsible for the project by symptoms such as redness, swelling, warmth, and soreness. Additionally mild pain from the site of the biopsy can be experienced within the first few days after the procedure has been performed, equivalent to a muscle rupture. There is a minimal risk of damaging the small nerves in the skin, causing numbness in a small area on the skin. Sense of touch is often back after a shorter or rarely longer period of time. We also have had two cases of damage to a motor nerve in the muscle, which has resulted in local muscle atrophy without affecting muscle function.

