**Design:**

• The subjects will be randomly allocated to one of the following 4 groups (10 persons in each group)

o Placebo treatment

o Placebo treatment + endurance training

o rHuEpo treatment

o rHuEpo treatment + endurance training

• Subjects are examined before and after 10 weeks rHuEpo/placebo treatment and again after a 3 weeks washout period.

• EPO (~50IU/kg)/placebo (saline) is administered using a small syringe under the skin twice a week for the first 3 weeks at a dosage of 2x 40μg, and once a week from week 4-12 at a dosage of 20μg.

• The endurance training will consist of 1 to 1.5 hours of cycling at 65-80% of maximum oxygen uptake, 3 times weekly.

 
[figure not shown]

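### The study-drug regimen is stated inconsistently: one IU/kg label covers two phases whose injections differ twofold, and the main text and layman description end dosing in different weeks

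*Protocol*

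**What the plan says.** The Protocol gives the regimen in two places.

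- **DESIGN (main text).** "EPO (Darbepoietin alpha) (~50IU/kg)/placebo (saline) is administered s.c. twice a week for the first 3 weeks at a dosage of 2x40" micrograms, then "once a week from week 4-10 at a dosage of 20" micrograms. The same section states the length of treatment: "Subjects are examined before and after 10 weeks of rHuEpo/placebo treatment, and after a 3 weeks washout period".
- **Layman description, Design.** "EPO (~50IU/kg)/placebo (saline) is administered using a small syringe under the skin twice a week for the first 3 weeks", with the same 2x40 micrograms, then 20 micrograms once a week. Here the weekly phase runs from week 4 to week 12. The bullet just above it still gives 10 weeks of treatment followed by a 3-week washout.

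Two other places fix the calendar. The blood-loss paragraph of SAFETY and the blood-test paragraph of the layman METHODS both put day 71 in the treatment period and days 78 and 92 in washout. The Serum paragraph of METHODS schedules the primary endpoint, serum proteomics, at baseline and on days 21, 71 and 92.

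The Protocol gives no conversion from IU to micrograms and no reference body weight.

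**The concern.** There are three separate faults in the dosing text.

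1. The IU/kg label appears once, ahead of two phases with different microgram amounts. A reader cannot tell which phase it describes, or whether it is a dosing rule or only a rough equivalent.
2. The two versions of the regimen disagree on the last dosing week.
3. The multiplier in 2x40 stands beside a frequency of twice a week, so it can be counted once or twice.

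These figures set the exposure of healthy volunteers to a drug for which SAFETY itself names thrombosis, hypertension and iron deficiency as risks of prolonged use. They also define the treatment being compared. The last dosing week determines whether the day 71 proteomics sample is taken at the end of treatment or during it, and how long after the last dose the day 92 sample is taken.

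**Working it through.** **Inputs.** From DESIGN: label of about 50 IU/kg; two administrations a week for 3 weeks, 2x40 micrograms; 20 micrograms once a week, weeks 4 to 10. From the layman Design: the same, but weeks 4 to 12. From the inclusion criteria: BMI 18 to 27. From SAFETY and METHODS: sampling days 71, 78 and 92.

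**1. Can the label be reproduced?** No. For an injection of D micrograms, IU/kg = D × c / w, where c is IU per microgram and w is weight in kg. Neither is given.

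The comparison between phases needs neither. In one man, c and w cancel:

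- per injection: 40 / 20 = 2
- per week: (2 × 40) / 20 = 4

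So the label cannot fit both phases, whether it is read per injection or per week.

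As an illustration only, assume an 80 kg man. Then 50 IU/kg is 50 × 80 = 4000 IU. This equals 20 micrograms if c = 4000 / 20 = 200, and 40 micrograms if c = 4000 / 40 = 100. One drug cannot have both conversions. Over assumed ranges of c from 100 to 400 and w from 60 to 90 kg, 20 micrograms is 22 to 133 IU/kg and 40 micrograms is 44 to 267 IU/kg. These ranges are too wide to show which phase was meant.

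**2. Fixed or weight-based?** At a given height, BMI 18 to 27 allows weights that differ by 27 / 18 = 1.5. A fixed injection then differs 1.5-fold per kg between the lightest and heaviest man of that height, and a per-kg dose differs 1.5-fold in micrograms. The text does not say which applies.

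**3. Course total, with 2x40 read as two 40-microgram injections a week.**

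| | Main text | Layman description |
|---|---|---|
| Loading | 2 × 40 × 3 = 240 | 240 |
| Weekly doses | 10 − 4 + 1 = 7 | 12 − 4 + 1 = 9 |
| Weekly phase | 7 × 20 = 140 | 9 × 20 = 180 |
| Total (micrograms) | 380 | 420 |

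The difference is 40 micrograms, or 40 / 380 = 10.5%.

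**4. Calendar check.** Assume day 1 is the first dosing day, so that week k starts on day 7(k − 1) + 1. Week 10 is then days 64 to 70, week 11 starts on day 71 and week 12 is days 78 to 84. Also 92 − 71 = 21 days, which matches the stated 3-week washout counted from day 71. A week 12 injection would fall within the period that the Protocol calls washout. The day 92 sample would come 92 − 84 = 8 to 92 − 78 = 14 days after the last dose. With dosing to week 10 it comes 92 − 70 = 22 to 92 − 64 = 28 days after.

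**5. The less natural reading of 2x40.** If 2x40 micrograms is given at each of two weekly administrations, loading is 2 × 80 × 3 = 480 micrograms, against 240 (ratio 2.0). Course totals become 480 + 140 = 620 (620 / 380 = 1.63) or 480 + 180 = 660 (660 / 420 = 1.57).

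**The case against.** The best defence is that the operative instruction is the fixed microgram amount in each phase. The IU/kg figure carries an approximation sign, appears once ahead of the loading clause, and may be only a rough equivalent for that phase. If so, the figures can coexist. That is a fair reading, but the text does not state it, and an approximation sign does not cover a factor of two. What stands is that the label need not be a competing dosing rule.

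Several stronger conclusions are tempting, and the documents do not support them.

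- **That the loading dose is doubled, or equally likely to be.** The two clauses run in parallel: a frequency, then the matching amount. The 2 in 2x40 most naturally restates twice a week, and no section mentions paired injections or 80 micrograms at one visit. This is loose wording and not a contradiction.
- **That the label is wrong by 2 to 4 times for one phase.** This assumes that it is right for the other, which cannot be shown without a conversion. The fourfold figure per injection also needs the less natural reading of 2x40.
- **That staff would give different doses within an arm.** Nothing in the Protocol describes how dosing is divided among staff.
- **That the safety precedent fails.** SAFETY says "A protocol similar to the Epo treatment regimen used here, has previously been approved", but the doses in those earlier studies are not given. The comparison could not be checked from this document even if the present dose were stated perfectly.

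The Protocol also has safeguards: haematology and blood pressure on the sampling days, including days 8, 15 and 21, and discontinuation above a haematocrit of 55%. These limit the consequences but do not settle the wording. The figure after the design bullets could not be read here. It may show the injection schedule, but it would not remove the conflict between the two written versions.

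**Conclusion.** The regimen text is inconsistent and needs correction, on narrower grounds than a doubled dose. Two faults are firm.

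- One IU/kg label cannot describe two phases whose injections differ at least twofold. This needs no assumption about weight or unit conversion.
- The last dosing week is 10 in one section and 12 in the other, and the later one conflicts with the 10-week treatment period and the washout days that the layman description itself states. The size is 7 or 9 weekly doses and 380 or 420 micrograms in total, on the natural reading of 2x40. The interval from last dose to the day 92 sample is 22 to 28 days or 8 to 14 days, if day 1 is the first dosing day.

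A third fault is minor: 2x40 is loosely worded, and only an unlikely reading takes the loading amount from 240 to 480 micrograms. The documents do not establish which dose or duration is intended, and none is endorsed here.

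**What to change.** The sponsor should reconcile the dosing bullets in DESIGN and in the layman Design so that both sections:

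- give the same amount per injection, number of injections per week and last dosing week for each phase, in one unit;
- state whether the dose is fixed or weight-based;
- either drop the IU/kg label or attach it to a named phase;
- replace 2x40 with an amount per injection and a separate frequency, so that the multiplier cannot be counted twice.

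The last dosing week should then be checked against the stated treatment length and the days labelled as washout. The choice of figures is the sponsor's.

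The cost is a text correction in two places. Sample size, visit schedule and analysis need no change if the reconciled dosing period fits the existing calendar.
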